### Outcomes

Outcome measures will be taken at base line just after enrolment, as well as at 4 weeks, 3 months and 6 months following treatment commencement by an assessor, blind to group allocation and intervention. To assess whether the participants were blind to intervention or not, after each treatment session the participants in the MMT and the placebo group will complete a questionnaire on whether they believed MMT treatment was received, partly received or not.

The primary outcome measure is headache frequency [46] which is the total number of headache days per month noted in a headache diary. Secondary outcome measures are as follows: headache intensity [47] recorded on a 10 cm visual analogue scale, which is considered a valid and reliable tool for measuring pain intensity [47]. Headache duration [46] will be measured in hours per week. Headache frequency and duration are considered a valid method of measurement in the headache population [46]. Medication Intake will be recorded as total tablets consumed per week. PPT will be measured using a digital algometer with a surface area of 1 cm kg/cm^2^, with pressure applied at the rate of 1 kg/ cm^2^ /s perpendicular to the skin. PPT will be assessed over the suboccipital muscles, C2–3 zygapophyseal joint and upper trapezius muscle bilaterally [48] to assess local hypersensitivity, and over the tibialis anterior muscle to assess central sensitisation. Reliability for measuring PPT was reported as excellent (ICC: 0.82–0.99) [49]. Headache disability will be recorded with the Headache Activities of Daily Living Index (HADLI) [50] which is a 9 item self-reported questionnaire designed to measure the impact of headache on quality of life. Each item has 6 sub-questions which are rated from 0 to 5 thus the maximum score of 45 indicates a severe disability. Patient satisfaction will be assessed using a 0–100% numeric rating scale. Passive upper cervical rotation range in degrees to both sides will be measured with the FRT using a previously reported reliable and valid method [45]. A compass application on a smart phone mounted on the patient’s head with Velcro straps will be used to measure range of motion. Reliability of the FRT was reported as good to excellent in subjects with migraine (0.71–0.78) and CGH (ICC: 0.73–0.83) [51].

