**Methods:**

This pragmatic trial is designed as a prospective, three-armed randomised controlled trial in a clinical setting provided at a general hospital physiotherapy department. Two hundred ninety-seven participants with a diagnosis of migraine, TTH or CGH based on published headache classification guidelines will be included. An assessor blind to group allocation will measure outcomes pre-and post-intervention as well as 3 and 6 months after commencement of treatment. Participants will be allocated to one of the three groups: MMT and exercise; placebo and exercise; and exercise alone. The primary outcome measure is headache frequency. Secondary outcome measures are headache duration and intensity, medication intake, pressure pain threshold (PPT), range of motion recorded with the flexion rotation test, and headache disability recorded with Headache Activities of Daily Living Index (HADLI). The intention-to-treat principle will be followed for statistical analysis. Between groups differences for all outcome measures at baseline and at reassessment points and 95% confidence intervals will be calculated using a mixed model ANOVA. Post hoc tests will be conducted to identify any significant difference between groups and over time.

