### Eligibility criteria

Consecutive participants with episodic migraine, episodic TTH and CGH referred to the physiotherapy outpatient department by the hospital medical department will be recruited into this trial. A diagnosis of episodic migraine, episodic TTH and CGH will be made by the primary investigator under the guidance of a medical practitioner as per the ICHD -3 [5]. Episodic TTH is at least 10 episodes of headache occurring on 1–14 days/month on average for > 3 months (≥12 and < 180 days/year) and lasting from 30 min to 7 days. Episodic migraine is that which occurs on less than 15 days per month for at least 3 months [5].

Participants will be included if they fulfil the following inclusion criteria: age more than 18 years and less than 60 years, pain intensity > 6 on a 10 cm visual analogue scale at the time of presentation (to balance headache severity across different headache groups), a minimum 1-year history of headache with a minimum mean frequency of 1 per week. This frequency was chosen to enable effective monitoring of outcome, in particular with respect to treatment intervention. Less frequent headache would make it difficult to monitor progress. An additional criterion is hypomobility of the upper cervical spine (C0–3) on manual examination. Manual examination has been shown to be reliable when used in the upper cervical spine [36], and has been used in previous studies exploring the effectiveness of manual therapy for headache [37–40]. By way of standardization, an upper cervical spine joint is classified as impaired if moderate or marked tissue resistance is perceived along with local or referred pain of > 2 on a 0–10 cm visual analogue scale on palpation [41]. A further criterion is the reproduction of headache on palpation of the upper cervical spine (C0–3) [29].

Participants will be excluded if their headache diagnosis is other than, migraine, TTH or CGH. In addition, exclusion criteria are instability of the upper cervical spine, evidence of cervical arterial insufficiency observed during clinical testing, history of vertigo or dizziness, rheumatoid arthritis, ankylosing spondylosis, cervical spine fractures, pregnancy, cognitive compromise, and any other contraindications to manual therapy.

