### Procedures

Participants will be provided with an information sheet outlining the study protocol including duration of commitment, intervention, benefits and harms of the treatment, voluntary participation, right to withdraw, as well as confidentiality of data. It will be explained that no compensation will be given if any adverse event occurs and study findings may be published but without revealing participants identity.

Those willing to participate will be enrolled and asked to provide signed written informed consent with the right to withdraw at any time. After recruitment, at initial assessment, a qualified therapist will explain the study procedures and collect demographic data. Confidentiality will be maintained throughout the trial.

Participants will then be randomly and equally allocated to one of three groups: MMT plus exercise; placebo plus exercise; or exercise alone by stratified randomization based on the type of headache. Randomization will be achieved using a computer-generated sequence received in advance from an independent statistician and will be hidden in sequentially numbered opaque sealed envelopes by a research assistant. All participants will be asked to not reveal their group identity and are advised to continue with their regular medical management. Any change in the protocol will be communicated with the ethics committee and if approved appropriate changes will be made in the Clinical Trial Registry.

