### Statistical methods

The sample size for this study was calculated based on the primary outcome of headache frequency. According to the International Headache Society guidelines (2018), a 50% reduction in headache frequency is considered a clinically significant difference. A sample size of 297 participants will be required for the study based on a priori power analysis with a power of 0.8 and an alpha of 0.05 assuming 10% drop-outs.

All data entry will be carried out by research assistants who will be blind to treatment allocation. The final trial dataset will be accessible to all investigators and a statistician. Data will be stored with the principal investigator. Descriptive statistics will be performed to examine baseline parameters and demographic data. Demographic data will include age, gender, symptom duration, occupation, height, and weight. Baseline parameters will include the headache frequency, intensity, duration, medication intake, PPT, HADLI score, and FRT range of motion. Parametric tests will be used for normal distributions and ratio level data. Between groups differences for the primary and secondary outcome measures at baseline and at reassessment points and 95% confidence intervals will be calculated using mixed ANOVA. Post hoc tests will be conducted to identify any significant difference between groups and over the time. The intention-to-treat principle will be used if loss of follow up is not more than 10%. Non-parametric tests will be applied for non-normal distributions and ordinal level data.

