## Discussion

To our knowledge, this will be the first pragmatic RCT to evaluate the effects of MMT in the management of migraine, TTH and CGH. A pragmatic effectiveness study design will enable a greater understanding of the true effect of MMT when compared with a placebo intervention and a control group in reducing various parameters of headache over a 6 months period. A placebo effect is associated with all physiotherapy interventions however its contribution may vary. This study will help us to understand the true net effect of MMT over placebo.

Recruitment will be a challenge due to the strict inclusion criteria but that could be strength of our study to involve a homogeneous population of headache sufferers with features of upper cervical articular dysfunction who might respond to MMT.

Previous studies using MMT targeting the upper cervical spine for headache management have not reported adverse events associated with its application. Thus this approach appears to be safe for its clinical use [52]. All participants will continue to take their medications as prescribed by their medical practitioner.

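### Medication intake counts all tablets together, so scheduled tablets that continue in every arm are pooled with the as-needed tablets the treatment could change

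*Protocol article*

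**What the plan says.** The Outcomes section lists medication intake among the secondary outcomes and defines it in a single sentence: "Medication Intake will be recorded as total tablets consumed per week". It draws no line between drug classes, or between tablets taken when a headache occurs and tablets taken on a schedule.

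Two other places deal with concurrent medication. Under Procedures, participants are "advised to continue with their regular medical management". The Discussion adds: "All participants will continue to take their medications as prescribed by their medical practitioner".

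The Eligibility criteria ask for "a minimum 1-year history of headache with a minimum mean frequency of 1 per week" but set no condition on current medication or on how stable it is.

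Under Statistical methods, medication intake is one of the baseline parameters: "Baseline parameters will include the headache frequency, intensity, duration, medication intake, PPT, HADLI score, and FRT range of motion". Between-group differences for primary and secondary outcomes "at baseline and at reassessment points and 95% confidence intervals will be calculated using mixed ANOVA", with post hoc tests between groups and over time. Reassessment is at 4 weeks, 3 months and 6 months after treatment starts.

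**The concern.** If the treatment reduces headache days, the tablets that should fall are those taken because a headache is present. Tablets taken on a schedule need not follow headache days, and the article says that prescribed medication continues. Adding the two gives a total in which only one part is expected to respond to MMT.

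Two things are at stake. First, differences in scheduled use between participants add variance to every single-visit comparison between arms. Second, a practitioner may start or stop a daily drug during the 6 months. One such change moves the weekly total by 7 tablets, and the total cannot show whether it came from that or from a change in as-needed use. A difference between arms would then be hard to read. Because only the total is recorded, no later analysis can separate the parts.

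**Working it through.** The article gives no mean, SD or prevalence for any kind of medication, so there is no stated figure to reproduce. The sample size of 297 was set on headache frequency and does not bear on this outcome. All tablet figures below are assumptions. Only the arm size (297 / 3 = 99, or about 89 after the stated 10% drop-out) comes from the article.

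**1. Single-visit comparison, scheduled use stable**

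Assume as-needed use has SD 2 tablets/week (variance 4). A share p of participants also take one daily tablet (7/week), independently of as-needed use.

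SD of total = √(4 + 49·p·(1 − p))

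- p = 0: √4 = 2.00
- p = 0.10: √(4 + 4.41) = 2.90
- p = 0.30: √(4 + 10.29) = 3.78

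**2. The same comparison as power, under a second set of assumptions**

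As-needed mean 4 tablets/week, SD 3, between-arm difference 1.3, 89 per arm, two-sided 0.05, pairwise. The SD of the total is √(9 + t²·q·(1 − q)), where a share q take t scheduled tablets per week.

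| Share q | t = 7/week: SD, power | t = 14/week: SD, power |
|---|---|---|
| 0 | 3.00, 0.82 | 3.00, 0.82 |
| 0.10 | 3.66, 0.66 | 5.16, 0.39 |
| 0.25 | 4.26, 0.53 | 6.76, 0.25 |
| 0.50 | 4.61, 0.47 | 7.62, 0.21 |

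**3. Change from baseline, scheduled use constant**

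A constant count is subtracted from itself within each participant, so the scheduled part adds nothing. With an as-needed SD of change of 3 (SD 3, pre/post correlation 0.5), power is 0.82 for every q and t above. There is no loss.

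**4. Change from baseline, some scheduled drugs started or stopped**

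Let a share c of participants start or stop one daily tablet, with starts and stops balanced and independent of as-needed use. The added variance is 49c.

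- As-needed variance of change 4 (SD 2, pre/post correlation 0.5): the variance ratio is (4 + 49c)/4. c = 0.05 gives 6.45/4 = 1.61; c = 0.15 gives 11.35/4 = 2.84.
- As-needed variance of change 9: c = 0.05 gives 11.45/9 = 1.27; c = 0.15 gives 16.35/9 = 1.82. For the 1.3-tablet difference with 89 per arm, power falls from 0.82 to about 0.73 and 0.57.

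**5. Could a few changes shift an arm mean materially?**

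Three net starts of a daily tablet in one arm of 99 move its mean by 3 × 7 / 99 = 0.21 tablets/week. Offsetting a 1.5-tablet effect would take 1.5 × 99 / 7 ≈ 21 net starts in one arm (about 19 with 89 per arm).

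**The case against.** Several objections limit the point, and most of them stand.

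- **No evidence of heavy scheduled use.** The article never mentions preventive drugs and gives no tablet counts. A reader might infer that preventive tablets swamp as-needed use, or that the outcome cannot answer whether MMT lowers the need for medication. Neither is supported. With SD 3.78 and a 1.5-tablet difference, single-visit power is still 0.80 with 99 per arm. With a 0.75-tablet difference it drops from 0.75 to 0.29. The outcome of this argument depends on unknown inputs.
- **Cancellation.** Medication intake is measured at baseline, so stable scheduled use drops out of the group-by-time contrast. This stands fully. It does not cover the planned comparisons at individual reassessment points, and nothing in the article ensures that scheduled use stays stable for 6 months.
- **Percentage dilution.** A reader might note that halving 3 as-needed tablets looks like a fall from 10 to 8.5, or 15%, in someone who also takes one daily tablet. The plan compares absolute differences between groups, and a fall of 1.5 tablets is 1.5 either way. This figure is not a flaw in the planned analysis.
- **A few regimen changes could create or erase a difference.** Step 5 of the working shows that they could not erase an effect of that size.
- **Total drug burden is a legitimate pragmatic measure.** A scheduled drug may be stopped because headaches eased, and an as-needed-only count could credit MMT when a new scheduled drug did the work. This is a fair reason to keep the total in view. It is also a reason to record the two parts, since the total alone cannot show which happened.
- **The article is condensed.** The full protocol or diary form may say which tablets count. The sentence in the article nevertheless says all tablets. If a fuller document restricts the count, one clarifying sentence settles the point.

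**Conclusion.** The point holds in a limited form. The stated definition pools scheduled and as-needed tablets while prescribed medication continues. The consequence is noise and ambiguity, not expected bias, because the medication instruction is the same in all randomised arms.

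The size cannot be fixed from the article. Under the assumptions shown, the single-visit SD rises from 2.0 to 2.9–3.8 when 10–30% take one daily tablet. The group-by-time contrast loses nothing if scheduled use is constant. If 5–15% start or stop a daily tablet, the variance of change rises by a factor between 1.27 and 2.84, depending on the variance assumed for as-needed change. These figures assume that scheduled use is independent of as-needed use.

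One secondary outcome is affected; the primary outcome and the sample size are not. It is a minor point, worth acting on because the remedy is cheap and the split cannot be recovered from totals afterwards.

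**What to change.** In the headache diary already used for the primary outcome, and in the baseline record, enter as-needed headache medication separately from regularly scheduled medication. Define the medication outcome as as-needed use, in tablets or in days with as-needed medication, and analyse it as planned. Report total tablets, and starts, stops and other changes in scheduled medication, by arm as description, so that overall drug burden stays visible and a fall in as-needed use can be read alongside any change in scheduled drugs.

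The cost is about one diary column, one sentence in the outcome definition and slightly more burden for participants. The change concerns measurement only and alters no participant's treatment.

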### Statistical methods

The sample size for this study was calculated based on the primary outcome of headache frequency. According to the International Headache Society guidelines (2018), a 50% reduction in headache frequency is considered a clinically significant difference. A sample size of 297 participants will be required for the study based on a priori power analysis with a power of 0.8 and an alpha of 0.05 assuming 10% drop-outs.

All data entry will be carried out by research assistants who will be blind to treatment allocation. The final trial dataset will be accessible to all investigators and a statistician. Data will be stored with the principal investigator. Descriptive statistics will be performed to examine baseline parameters and demographic data. Demographic data will include age, gender, symptom duration, occupation, height, and weight. Baseline parameters will include the headache frequency, intensity, duration, medication intake, PPT, HADLI score, and FRT range of motion. Parametric tests will be used for normal distributions and ratio level data. Between groups differences for the primary and secondary outcome measures at baseline and at reassessment points and 95% confidence intervals will be calculated using mixed ANOVA. Post hoc tests will be conducted to identify any significant difference between groups and over the time. The intention-to-treat principle will be used if loss of follow up is not more than 10%. Non-parametric tests will be applied for non-normal distributions and ordinal level data.

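### Baseline is analysed as one of four occasions instead of being adjusted for, and the primary method depends on the observed distribution: this costs precision and leaves the effect estimate open

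*Protocol article*

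**What the plan says.** The primary outcome is a monthly count (Outcomes): "The primary outcome measure is headache frequency [46] which is the total number of headache days per month noted in a headache diary". It is measured "at base line just after enrolment, as well as at 4 weeks, 3 months and 6 months following treatment commencement", which makes four occasions.

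Statistical methods states that differences between groups "at baseline and at reassessment points and 95% confidence intervals will be calculated using mixed ANOVA". The Abstract agrees: "Between groups differences for all outcome measures at baseline and at reassessment points and 95% confidence intervals will be calculated using a mixed model ANOVA". Next comes "Post hoc tests will be conducted to identify any significant difference between groups and over the time". No baseline covariate, stratum term, primary visit or primary contrast is given, although Procedures says that randomisation is stratified by headache type.

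The same section makes the method conditional on the data: "Parametric tests will be used for normal distributions and ratio level data", and "Non-parametric tests will be applied for non-normal distributions and ordinal level data". It does not say which non-parametric test, what decides that a distribution is non-normal, or what effect estimate would go with the test.

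**The concern.** Two features of the stated method raise the issue.

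First, baseline enters as a level of time. No treatment effect can exist there, so a group main effect over all four occasions is pulled towards zero. The group-by-time contrast at a visit becomes a comparison of change scores. A plain comparison at a follow-up visit makes no use of baseline at all. None of these uses the collected baseline as well as adjusting for it would.

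Second, the analysis of the primary outcome is settled only after its distribution has been seen. Headache days per month cannot go below zero or above the length of the month. Eligibility narrows the range at entry: at least one headache per week on average, and fewer than 15 days per month for episodic migraine and TTH. The primary hypothesis of a 50% reduction would push counts towards zero. A skewed count on a ratio scale is a likely candidate for the non-normal branch. In that branch the plan no longer fixes an adjusted difference in headache days with its interval.

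At stake are the precision of the MMT comparisons and whether the reported effect measure is known in advance.

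**Working it through.** **The plan's own figure.** "A sample size of 297 participants will be required for the study", at power 0.8, alpha 0.05 and 10% drop-out. This cannot be reproduced, because no SD, between-group difference or test is given. Only the drop-out step can be inverted: 89 × 3 = 267, and 267 / 0.90 = 296.7, rounded up to 297. (270 × 1.10 = 297, or 90 per arm, fits too and changes little.)

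**Assumptions not in the documents.**
- Two-sided alpha 0.05 and a two-group comparison with 89 per arm.
- Standardised difference d that this n detects with 80% power: d = √(2/89) × (1.960 + 0.842) = 0.42.
- Baseline-to-follow-up correlation r of 0.3, 0.5 or 0.7, equal between all occasions. The Discussion says that recall bias may affect baseline while the outcome comes from a diary, so a low r cannot be excluded.
- For averages over visits, an effect that is constant from the first follow-up.

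**Formulas.** Power = Φ(effect × √(89/2) / √V − 1.96), where V is the variance per participant in units of σ².
- Change from baseline at one visit: V = 2(1 − r)
- Follow-up only at one visit: V = 1
- Baseline-adjusted at one visit: V = 1 − r²
- Group main effect over four occasions: effect 0.75d, V = (1 + 3r)/4
- Mean of three follow-ups, unadjusted: V = (1 + 2r)/3
- Mean of three follow-ups, baseline-adjusted: V = (1 + 2r)/3 − r²

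Example, change at r = 0.3: 0.42 × √44.5 = 2.80; 2.80/√1.4 = 2.37; Φ(2.37 − 1.96) = 0.66.

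| Power | r = 0.3 | r = 0.5 | r = 0.7 |
|---|---|---|---|
| *One visit* | | | |
| Change | 0.66 | 0.80 | 0.95 |
| Follow-up only | 0.80 | 0.80 | 0.80 |
| Baseline-adjusted | 0.84 | 0.90 | 0.98 |
| *Averaged over visits* | | | |
| Group main effect, baseline included | 0.86 | 0.76 | 0.67 |
| Mean of three follow-ups, unadjusted | 0.97 | 0.93 | 0.88 |
| Mean of three follow-ups, adjusted | 0.99 | 0.99 | >0.99 |

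The two blocks must be read separately, since an average over visits is a different target from a single visit.

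**Relative variance.** Change against adjusted: 2/(1 + r) = 1.54, 1.33, 1.18. Follow-up only against adjusted: 1/(1 − r²) = 1.10, 1.33, 1.96. For 80% power at one visit, the analysable n per arm is 125, 89 and 54 for change, 89 for follow-up only, and 81, 67 and 46 with adjustment.

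**Simulation check.** In 2,000 simulated trials per r with normal data, power was 0.66/0.79/0.95 for change, 0.81 throughout for follow-up only, and 0.84/0.90/0.97 adjusted. A Mann-Whitney test on follow-up values had 0.79 to 0.80, so switching to ranks costs little power on normal data.

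**The case against.** The strongest reply is that this is a matter of efficiency, not an error. Under randomisation the between-arm contrasts at follow-up and in change are unbiased, and covariates are often left to an analysis plan that is not shown. The first part stands: a reader might infer that the mixed ANOVA gives biased contrasts, and it does not. The second stands only in part, because the protocol does state a method, the treatment of baseline within it and a rule for changing it.

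The size of the loss is also open to dispute. Read literally, differences at the reassessment points are follow-up-only contrasts. At r = 0.3 the loss is then 0.80 against 0.84, not 0.66 against 0.84. The protocol does not say which contrast decides. Nor is change always a poor choice: at r = 0.7 it is well ahead of ignoring baseline.

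Four further inferences are tempting but unsupported:
- **That participants with a missed visit are dropped.** A classical repeated-measures ANOVA would do so, but the Abstract's term can equally mean a mixed model on all available data.
- **That non-parametric tests rule out adjustment or an interval.** Hodges-Lehmann intervals, stratified rank tests (van Elteren), rank ANCOVA and non-parametric factorial methods exist. The fault is that none is named.
- **That baseline significance tests are planned.** The text speaks of calculating differences and intervals at baseline, and separately plans descriptive statistics.
- **That 0.42 SD is the trial's design effect.** It is back-solved here.

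**Conclusion.** The point holds as one of precision and pre-specification. The plan as written loses precision in whichever single-visit contrast is read. Baseline adjustment does better than both at each assumed correlation: by 0.03 to 0.18 in power against change, and by 0.04 to 0.18 against follow-up only. If the group main effect is read, it estimates 0.75 of a constant effect, with power 0.67 to 0.86 against about 0.99 or more for the baseline-adjusted mean of the follow-ups. These figures rest on the assumed r, the back-solved d, equal correlations and a constant effect. The ordering of the three single-visit contrasts, with adjustment first, does not depend on d.

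The normality switch is a separate weakness. It makes the primary method depend on the data and leaves the effect estimate undefined in a branch that may well apply. Its cost is the lost estimate rather than power. The point should be acted on, but it does not invalidate the trial.

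**What to change.** Replace the mixed ANOVA and the switching rule with one pre-specified longitudinal model for headache days:
- Outcome values at 4 weeks, 3 months and 6 months, using all available data.
- Terms for arm, visit, arm-by-visit, baseline value, baseline-by-visit and headache type.
- Adjusted differences with 95% CIs for MMT plus exercise against each of the two controls, at one named primary visit.
- No choice of test on observed normality. Keep the model, use robust or bootstrap CIs, and add a count model suited to a bounded count as a sensitivity analysis.
- Baseline presented descriptively only.

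The cost is analysis wording and a little analyst time. No extra data or participants are needed.

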This paper aims to report the study protocol which will be used to investigate the short and mid-term effectiveness of MMT and exercise on headache frequency, intensity, disability, and duration as well as medication intake, upper cervical rotation range of motion, PPT and patient satisfaction compared with placebo and exercise and exercise alone in the management of migraine, TTH, and CGH. The objective is to investigate whether MMT with exercise is more effective than placebo MMT with exercise or exercise alone. Our primary hypothesis is that there will be a 50% reduction in headache frequency in the experimental group (MMT with exercise) and recovery is greater than that seen in the 2 control groups (placebo MMT with exercise and exercise alone).

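### Headache frequency has no primary time point and its two primary comparisons have no order or joint rule, so the single alpha of 0.05 is tied to no one test

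*Protocol article*

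**What the plan says.** All places are in the protocol article.

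- **Background (aim and primary hypothesis):** headache frequency is expected to halve in the MMT-plus-exercise arm, and "recovery is greater than that seen in the 2 control groups", that is, placebo plus exercise and exercise alone. The aim covers short-term and mid-term effectiveness and ranks neither first.
- **Procedures:** "Participants will then be randomly and equally allocated to one of three groups", so there are three pairwise comparisons.
- **Outcomes:** "Outcome measures will be taken at base line just after enrolment, as well as at 4 weeks, 3 months and 6 months". The primary outcome is headache days per month from a diary, with no visit attached to it.
- **Statistical methods (size):** the total of 297 is said to be "based on a priori power analysis with a power of 0.8 and an alpha of 0.05 assuming 10% drop-outs". One alpha is stated, without a comparison or visit to which it belongs.
- **Statistical methods (analysis):** group differences at baseline and at each reassessment come from a mixed ANOVA, and "Post hoc tests will be conducted to identify any significant difference between groups and over the time". The post hoc procedure is not named. Nothing says whether it is adjusted, or conditional on the ANOVA. The Abstract gives the same plan.

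**The concern.** The primary hypothesis names two comparisons, but the only tests that address them individually are post hoc tests looking for any difference. With three follow-up visits there are 2 × 3 = 6 tests of MMT against a control, and 3 × 3 = 9 between-group tests in all. If the visits disagree, for example a benefit at 4 weeks that is gone by 6 months, nothing in the article says whether the trial succeeded. The same holds if MMT beats exercise alone but not placebo.

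The choice of correction could sit in a statistical analysis plan. The primary visit and the rule for the two primary comparisons define the main question and what the sample size is for, so they belong in the protocol.

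The tests over time raise a second issue. Every arm receives the exercise programme, and entry requires pain above 6 on a 10 cm scale at presentation, so pain at least is likely to fall in all arms. Change within the MMT arm says nothing about what MMT adds. The hypothesis of a 50% reduction in that arm nevertheless invites this reading.

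**Working it through.** **1. The plan's own figure.** 297/3 = 99 per arm, and 99 × 0.9 = 89.1 after the stated 10% drop-out. No baseline mean, SD or control-group change is given, so 297 cannot be reproduced, only back-solved:

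- One pairwise comparison at one visit, two-sided 0.05, power 0.80: n = 2(1.960 + 0.842)²/d². With d = 0.42, n = 2 × 7.85/0.1764 = 89 per arm; 3 × 89 = 267; 267/0.9 = 297.
- Three-group omnibus ANOVA with f = 0.19: 270 in total; 270 × 1.1 = 297.

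Both effect sizes were chosen to hit the target, so neither is evidence of what was done. The total fits a single pairwise test and an omnibus test equally well, and so does not show where the alpha is spent.

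**2. Inputs for the error rate.** From the article: three equal arms, three post-baseline visits, alpha 0.05. Assumed: two-sided tests, approximately normal arm means, no true difference anywhere (global null), and the same correlation ρ between any two visits. The article gives no ρ, so 0.3 to 0.9 is shown.

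**3. Formula.** For arms j and k at visit t, Z = (mean_jt − mean_kt)/(σ√(2/n)). Two contrasts that share an arm at the same visit have correlation 0.5 in absolute value. The same contrast at two visits has correlation ρ. If all tests were independent the family-wise rate would be 1 − 0.95^k, which is 0.26 for k = 6 and 0.37 for k = 9. These are upper benchmarks. The dependent case was simulated with at least 400,000 runs per entry (standard error below 0.001).

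**4. Chance of at least one false positive on headache frequency, global null:**

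| Reading of the plan | ρ = 0.3 | 0.5 | 0.7 | 0.9 |
|---|---|---|---|---|
| Nine between-group tests, unadjusted, ungated | 0.31 | 0.28 | 0.25 | 0.20 |
| Six MMT-vs-control tests, unadjusted, ungated | 0.24 | 0.22 | 0.19 | 0.15 |
| Tukey over the three pairs at each visit | 0.14 | 0.13 | 0.11 | 0.09 |
| Nine tests, only if the group or the group × time F test is significant (four visits with baseline) | 0.08 | 0.08 | 0.07 | 0.06 |
| Nine tests, only if one overall test across groups and visits is significant | 0.05 | 0.05 | 0.04 | 0.04 |
| MMT differs from both controls in the same direction at the same visit, any visit | 0.03 | 0.03 | 0.02 | 0.02 |

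**5. Beyond the global null.** Suppose MMT truly beats exercise alone by a wide margin at every visit but equals placebo. An overall gate then nearly always opens, and the both-controls rule reduces to three looks at MMT versus placebo. That is 0.14 to 0.08 two-sided for ρ = 0.3 to 0.9, of which half (about 0.07 to 0.04) favours MMT, against a nominal 0.025. The low figures in the last two rows therefore do not remove the need for one primary visit.

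**6. With one visit fixed.** Two unordered, unadjusted contrasts give 0.09. In fixed order the second is tested only after the first succeeds, so the rate is at most 0.05.

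**The case against.** The strongest objection is that the article never says the post hoc tests are unadjusted or ungated. Post hoc tests after an ANOVA often carry a correction or follow a significant F test, and the name of the procedure is a detail a journal article may leave to the analysis plan. This stands. A reader might infer that the plan as written carries a 20–30% false-positive rate. The text does not support that as an unconditional figure.

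A second objection also has force. A reader might infer that the trial can declare success from whichever test reaches 0.05. The post hoc sentence sets no success criterion, and the Background wording is most naturally read as requiring MMT to beat both controls, which gives 2–3% under the global null. Counting only results in favour of MMT also roughly halves the six-test figure, to about 0.07–0.12. However, the article does not state the both-controls rule as a test or attach it to a visit.

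Two further inferences should be resisted. Enrolment selects for high pain, but not clearly for high headache frequency: the frequency criterion is a mean of at least one per week, and episodic migraine and TTH are capped below 15 days a month. Placebo versus exercise is also not an idle contrast, since the Discussion takes an interest in how much the placebo effect contributes.

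None of this supplies a primary time point. Correcting within each visit leaves three visits open, and no standard correction says which visit counts when they disagree.

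**Conclusion.** The concern holds in conditional form. What is firm is that headache frequency has no primary visit, the two primary comparisons have no order or joint rule, and the stated alpha of 0.05 therefore belongs to no identified test.

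The size depends on what the unnamed post hoc procedure turns out to be: 15–24% (six tests) or 20–31% (nine tests) if unadjusted and ungated, about 9–14% with Tukey at each visit, and 5% or less under the global null with one overall gate or a both-controls rule at the same visit. These figures assume two-sided tests, normal means, equal arms and a between-visit correlation of 0.3 to 0.9. They cover the primary outcome only and exclude within-arm tests over time. Because the gap concerns the trial's main question, it should be closed before any unblinded analysis; a visit chosen afterwards cannot restore error control.

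**What to change.** Before any unblinded analysis, amend the protocol and the registry entry to:

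1. Name one primary time point for headache frequency. The choice is the sponsor's. Three months is only an example; its merit is that the diary month would lie wholly after the four weeks of treatment.
2. Replace the open post hoc search with two planned contrasts at that visit, by one of two rules. (a) Fixed order: MMT plus exercise versus placebo plus exercise at two-sided 0.05, then MMT plus exercise versus exercise alone at 0.05 only if the first is significant. (b) A stated requirement that both be significant.
3. Report the other visits, placebo versus exercise, and the secondary outcomes as estimates with 95% confidence intervals and no confirmatory claim.
4. State that within-arm change over time is not evidence of an MMT effect.

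**Cost.** The change is to wording. There would be no confirmatory claim from the other visits and, under (a), none on the second contrast if the first fails. If each contrast has 80% power, the chance that both succeed lies between 1 − 0.2 − 0.2 = 60% and 80%. Neither rule splits alpha. Splitting it at 0.025 each would, on the back-solved d = 0.42, need 2(2.241 + 0.842)²/0.1764 = 108 per arm, or 324/0.9 = 360 in total instead of 297. Since 297 cannot be reproduced, the sponsor should also confirm that it powers the chosen contrast at the chosen visit.
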